#### Control variables and covariates

To characterize the sample and ensure balance across groups in analyses for treatment effects, we will prospectively collect the following information from electronic medical records and parent report questionnaires to control for (1) major medical complications associated with prematurity, including GA, birth weight, sex, history of antenatal steroid usage, infection, number of days of intubation and oxygen, and X-ray changes consistent with chronic lung disease; (2) PMA at MRI scan; (3) the number of nights of exposure to study treatment; and (4) sociodemographic factors associated with later language outcomes, including the SES of primary caretakers as measured by the HI [43], the frequency and number of languages spoken by adult and child household members, and number of siblings.

We will also obtain metrics to ensure balance across groups on the basis of the amount of language exposure experienced by infants in their home environments. To collect data on naturalistic maternal/caregiver input during the infancy period, we plan to use the Language ENvironment Analysis (LENA) recording device and software [54]. Families will be asked to perform two full-day (16 h) home LENA voice-recording sessions immediately around the time of the 12 months AA visit for MRI scanning. From this device, we will examine the adult words count measure per hour, normalizing for the length of audio recording, since it is the most accurate measure from LENA at this age when the infants may have limited language production skills [55]. If the groups do not match, we will use this language exposure metric as a covariate in the analyses.

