### Analysis plan

#### Power calculations

We calculated the sample size based on power. The significance level is *p* < 0.05 for all analyses. Power estimates are based on the means, standard deviations, and samples size from an RCT neuroimaging study of preterm neonates that showed a significant effect of a parent-based NICU intervention on diffusion metrics measured at close-to-term age (Cohen’s *d* = 1.03) and developmental outcomes (Cohen’s *d* = 1.77) measured at 9 months AA [56]. Thus, if we assume an effect size that is more conservative than this earlier study, specifically Cohen’s *d* = 1.0, we will have a power of ß = 0.8, if we enroll a sample size of at least 17 participants per group. Therefore, our planned enrollment of 21 participants per group will yield a power of ß = 0.88 to detect an effect size at that level (Cohen’s *d* = 1.0). If our effect size is even smaller than we anticipate, for example, Cohen’s *d* = 0.9, a planned enrollment of 21 per group will still yield a power greater than 0.8 to detect a treatment effect.

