#### Analytic strategy

We anticipate that stratification prior to randomization will result in a close matching of T and C groups on demographic and health variables. Prior to statistical analyses, we will use independent samples t-tests (continuous variables) or chi-square tests (categorical variables) to assess the statistical balance between T and C groups on the basis of GA, sex, SES, clinical complications associated with premature birth, and language exposure during treatment and after hospital discharge. Analyses will use an intention-to-treat strategy [57]. If groups are matched on all variables, we will use independent t-tests (two-tailed) to compare T versus C groups on the primary long-term language outcome and the secondary short-term outcomes that relate to white matter development. Should groups not be balanced, and to account for missing data, we will use linear mixed models: T group as a fixed factor and unmatched or missing variables are random factors. Statistical significance is set at *p* < 0.05. Should an imbalance of twins or multiples occurs, we will perform group analyses including all singletons and one randomly selected twin or multiple from each set [58].

We will perform post hoc univariate and/or non-parametric analyses to determine if neural and clinical outcomes are associated with variations in the dose (i.e., number of hours of maternal speech delivered) or length (i.e., number of nights of delivery) of treatment, controlling for GA and PMA. Post hoc covariance analyses will permit further interpretation of either significant or non-significant treatment effects for short- and long-term neural and language outcomes. We will use multiple regression analyses to predict language outcomes from short-term neural and clinical outcomes, while controlling for group status and measures of language exposure.

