### Limitations of the study

The present intervention may not significantly change long-term language outcomes or white matter development. It is possible that parents who consent to the study may increase their verbal input to infants, thus swamping treatment effects. However, the amount of speech that neonates typically hear is generally limited and will be vastly increased by the proposed intervention. In addition, individual variations in language exposure following discharge from the NICU may swamp out early gains made by the NICU intervention. If we fail to find long-term effects of the intervention, it may be that naturalistic maternal speech overwhelms the effects of the intervention. Such findings would suggest a need for additional language interventions administered within the first postnatal year (e.g., monthly; every 3 months; quarterly) that could be developed and tested as part of future RCTs.

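### Language exposure measured after randomisation decides the treatment-effect model and enters it when the arms differ, which may remove part of the effect the trial sets out to estimate

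*Protocol article*

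**What the plan says.** Three parts of the protocol article bear on this.

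- **Control variables and covariates.** Families make two full-day home LENA recordings around the 12-month visit. The metric is adult words per hour. The rule is "If the groups do not match, we will use this language exposure metric as a covariate in the analyses".
- **Analytic strategy.** Before the outcome analysis, t-tests or chi-square tests compare the arms on gestational age (GA), sex, socioeconomic status (SES), clinical complications and "language exposure during treatment and after hospital discharge". Then: "If groups are matched on all variables, we will use independent t-tests (two-tailed) to compare T versus C groups", for both the primary language outcome and the short-term white matter outcomes. Otherwise a linear mixed model takes in the unmatched variables. The same section commits to intention-to-treat, and "Statistical significance is set at *p* < 0.05".
- **Background and Study design.** The aim is the causal effect of the randomised NICU intervention. The primary assessment is the parent-completed language questionnaire (CDI) at 18 months adjusted age.

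Nothing confines the balance check or the adjustment to variables fixed before randomisation. Nothing labels the exposure-adjusted model as a sensitivity or mediation analysis.

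**The concern.** A baseline imbalance in a randomised trial can arise only by chance. An imbalance in speech heard during or after treatment can arise by chance or because treatment produced it; for example, a more responsive infant may draw more talk from adults at home. A balance test cannot tell these apart, and the rule adjusts precisely when a difference appears.

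If treatment did shift exposure, the adjusted coefficient is no longer the total effect of assignment. It leaves out whatever runs through later exposure. It is also open to collider bias from unmeasured family factors that influence both home speech and the language score. Because the choice of model depends on the data, what the primary analysis estimates would not be settled until those data were seen.

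There is also a problem of timing. Matching on all variables governs the white matter comparisons too, and one of these uses the scan before discharge. As written, a LENA difference at 12 months would change the model for an outcome measured about a year earlier, which it cannot have confounded.

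**Working it through.** **Inputs from the article (Power calculations, Analytic strategy).** Two-sided alpha 0.05; d = 1.0; 17 per group for power 0.80; 21 per group for power 0.88; power above 0.80 at d = 0.9.

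**Assumptions, because the article gives no figure.** a = treatment shift in the exposure metric, in SD; b = change in outcome, in SD, per SD of exposure. Both are varied.

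**1. The plan's own figures.** Two-sample t-test, df = 2n − 2, noncentrality d√(n/2):

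- n = 17, d = 1.0: √8.5 = 2.915, power 0.807.
- n = 21, d = 1.0: √10.5 = 3.240, power 0.885.
- n = 21, d = 0.9: 0.9 × 3.240 = 2.916, power 0.812.

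All three stated figures reproduce. They apply to the unadjusted comparison.

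**2. Effect of adjusting.** Let exposure M = aT + error and outcome Y = (1 − ab)T + bM + error, with unit SD within arm. The total effect is (1 − ab) + ab = 1.0. Conditioning on M leaves 1 − ab:

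- a = 0.5, b = 0.3: 1 − 0.15 = 0.85
- a = 0.5, b = 0.4: 1 − 0.20 = 0.80
- a = 0.7, b = 0.3: 1 − 0.21 = 0.79
- a = 0.7, b = 0.4: 1 − 0.28 = 0.72

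**3. How often the rule fires.** This is the power of the balance test at effect a with 21 per arm: 0.05 at a = 0, 0.16 at 0.3, 0.35 at 0.5 and 0.60 at 0.7.

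**4. Average over all trials.** When the rule does not fire, the observed exposure difference is smaller than average, so the unadjusted estimate in those trials also averages below 1.0. At a = 0.5 the mean exposure difference in non-firing trials is 0.327 (simulated). For b = 0.3 they average 0.85 + 0.3 × 0.327 = 0.948. Overall: 0.353 × 0.85 + 0.647 × 0.948 = 0.913. For b = 0.4: 0.80 + 0.4 × 0.327 = 0.931, and 0.353 × 0.80 + 0.647 × 0.931 = 0.885.

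Simulation of the whole rule (20,000 to 40,000 trials per scenario, exposure entered by ANCOVA only if its t-test gives p < 0.05) gives, to within simulation error:

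| a | b | Fires | Estimate when it fires | Mean over all trials | Power |
|---|---|---|---|---|---|
| 0 | 0.3–0.5 | 5% | 1.00 | 1.00 | 0.89 |
| 0.3 | 0.3–0.5 | 16% | 0.91–0.85 | 0.96–0.94 | 0.86 |
| 0.5 | 0.3–0.4 | 35% | 0.85–0.80 | 0.92–0.88 | 0.82–0.80 |
| 0.7 | 0.3–0.4 | 60% | 0.79–0.72 | 0.84–0.79 | 0.73–0.69 |

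**5. Collider bias.** Take a true null effect, b = 0, and an unmeasured factor loading 0.6 on both exposure and outcome. The rule then gives a mean estimate of about −0.11 at a = 0.5 and −0.24 at a = 0.8, with type I error about 0.06 and 0.12. This also needs a above zero; at a = 0 the mean is zero and the error rate about 0.05.

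**The case against.** The strongest reply is that the harm is conditional. Families and staff are blinded, the recordings play at night when parents are unlikely to be present, and the metric counts adult words rather than infant vocalisation. The Limitations section treats later exposure as noise that could mask the effect ("individual variations in language exposure following discharge from the NICU may swamp out early gains made by the NICU intervention"), not as its product. If treatment does not move exposure, the rule costs nothing on average. This stands, and it limits how large a loss can be claimed. It does not rescue the rule, whose trigger cannot separate chance from consequence and which fires more often the more treatment has shifted exposure.

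Three stronger readings are tempting, and the article does not support them.

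- A reader might infer that infants without LENA recordings would be dropped. The article does not specify a complete-case analysis; it says mixed models are used partly to deal with missing data.
- A reader might infer that exposure during treatment differs between arms by design, because only one arm hears recordings. The article does not say that recordings count in this variable. It handles hours delivered separately, as a post hoc dose analysis, so natural speech is the more coherent reading.
- The Limitations sentence might be taken as part of the fault. It prescribes no adjustment.

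The planned regression of language outcomes on short-term outcomes, controlling for group and exposure, is a separate predictive analysis and is not at issue.

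**Conclusion.** The point holds as a fault in a stated rule. The article lets post-randomisation exposure decide, and then enter, the model for the treatment effect. It does not hold as a claim that the effect will be adjusted away: that requires treatment to change exposure, and the article gives neither that shift nor the slope to the outcome.

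On the assumptions above, the consequence runs from nothing at a = 0, through an average loss of about 4 to 6% at a = 0.3, to about 8 to 12% at a = 0.5 with b = 0.3 to 0.4. The corresponding 15 to 20% loss at a = 0.5 applies only to trials in which the rule fires, and should not be read as the overall loss. The effect on the pre-discharge white matter model follows from the wording alone and needs no assumption.

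**What to change.** - Delete the LENA covariate rule for the treatment comparison.
- Remove language exposure during treatment and after discharge from the balance list that decides the model.
- Adjust primary and secondary treatment effects only for variables fixed before randomisation, named in advance; the minimisation factors, GA and SES, are the natural choice.
- Report LENA and in-treatment exposure by arm as post-treatment measures, and use them only in an analysis labelled exploratory or mediation.

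The cost is a change of wording. LENA is still collected and reported and the sample size is unchanged. Without the exposure-triggered adjustment, the unadjusted comparison keeps the total effect as its target, with power of about 0.885 at d = 1.0 and 21 per group.

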### Analysis plan

#### Power calculations

We calculated the sample size based on power. The significance level is *p* < 0.05 for all analyses. Power estimates are based on the means, standard deviations, and samples size from an RCT neuroimaging study of preterm neonates that showed a significant effect of a parent-based NICU intervention on diffusion metrics measured at close-to-term age (Cohen’s *d* = 1.03) and developmental outcomes (Cohen’s *d* = 1.77) measured at 9 months AA [56]. Thus, if we assume an effect size that is more conservative than this earlier study, specifically Cohen’s *d* = 1.0, we will have a power of ß = 0.8, if we enroll a sample size of at least 17 participants per group. Therefore, our planned enrollment of 21 participants per group will yield a power of ß = 0.88 to detect an effect size at that level (Cohen’s *d* = 1.0). If our effect size is even smaller than we anticipate, for example, Cohen’s *d* = 0.9, a planned enrollment of 21 per group will still yield a power greater than 0.8 to detect a treatment effect.

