**Methods:**

This randomized controlled trial assesses the long-term effects of increased maternal speech exposure on structural connectivity at 12 months of age (age adjusted for prematurity (AA)) and language outcomes between 12 and 18 months of age AA. Study participants (*N* = 42) will include infants born very preterm (24–31 weeks 6/7 days GA). Newborns are randomly assigned to the treatment (*n* = 21) or standard medical care (*n* = 21) group. Treatment consists of increased maternal speech exposure, accomplished by playing audio recordings of each baby’s own mother reading a children’s book via an iPod placed in their crib/incubator. Infants in the control group have the identical iPod setup but are not played recordings. The primary outcome will be measures of expressive and receptive language skills, obtained from a parent questionnaire collected at 12–18 months AA. The secondary outcome will be measures of white matter development, including the mean diffusivity and fractional anisotropy derived from diffusion magnetic resonance imaging scans performed at around 36 weeks postmenstrual age during the infants’ routine brain imaging session before hospital discharge and 12 months AA.

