### Outcome assessment methods

The primary outcome is language development (domain) assessed through the MacArthur-Bates CDI (measure) at (metric) 18 months AA (time point), quantified as expressive and receptive language raw scores and aggregated as group means (aggregation). The secondary outcome is white matter development (domain) assessed through dMRI scans (measure) collected at (metric) two different time points (time point): (1) prior to hospital discharge (neonatal time point) and (2) at 12 months AA (1-year time point), quantified with the dMRI metric (MD) and aggregated as group means (aggregation).

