#### Neuroimaging pre-processing and tractography

We plan to use established pipelines for image pre-processing and tractography. These pipelines rely on a combination of open-source software, including mrDiffusion [48], Statistical Parametric Mapping [49], FMRIB Software Library [50], mrTrix3 [51], Advanced Normalization Tools [52], and Automated Fiber Quantification [53]. Pre-processing includes the alignment to T1-weighted anatomical scan, de-noising, and corrections for participant motion, eddy currents and EPI distortions, and model fitting to obtain the three eigenvalues (λ1, λ2, λ3) used to compute MD, FA, radial diffusivity, and axial diffusivity. Tractography procedures include steps for producing the whole-brain tractogram, segmentation of individual white matter fiber groups in native space, and estimation of diffusivity metrics within specified tract segments [53].

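### White matter is tested at a flat p < 0.05 at two ages, with MD as the metric in some sections and MD plus FA in the abstract, so false-positive risk is about 8–10% (MD) or 13–19% (MD and FA)

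*Protocol article*

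**What the plan says.** - **Threshold.** Power calculations: "The significance level is *p* < 0.05 for all analyses". Analytic strategy: "Statistical significance is set at *p* < 0.05". Neither section mentions a multiplicity adjustment, a testing order or a key diffusion comparison.
- **Test.** Analytic strategy: "we will use independent t-tests (two-tailed) to compare T versus C groups". If the groups are balanced, this covers the primary language outcome and the short-term white matter outcomes (in the plural).
- **Outcome definition.** Outcome assessment methods: "The secondary outcome is white matter development (domain) assessed through dMRI scans (measure"). It sets two time points, before discharge and 12 months adjusted age, and the outcome is "quantified with the dMRI metric (MD"). The last paragraph of the Background agrees: its specific hypothesis is lower MD in the treatment group.
- **Abstract.** The Methods paragraph gives the secondary outcome as white matter measures "including the mean diffusivity and fractional anisotropy", at the same two ages.
- **Processing.** The tractography section describes fitted eigenvalues "used to compute MD, FA, radial diffusivity, and axial diffusivity", followed by "estimation of diffusivity metrics within specified tract segments". The segments are neither named nor counted.

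**The concern.** A 0.05 threshold holds the error rate at 5% for one comparison. The outcome definition already contains two (MD at two ages), and on the abstract's reading four (MD and FA at two ages). If each is judged at 0.05, the chance that at least one is significant by luck exceeds 5%, and nothing in the text brings it back.

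The disagreement over the metric adds a separate problem. If MD is null and FA is not, the abstract supports calling FA a secondary outcome. If FA is null, Outcome assessment methods supports leaving it out. Both choices would be open after the data are seen. FA also has no stated direction, whereas MD has one.

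The result matters to the trial's message. White matter is the second of two aims, and the Discussion suggests that brain changes might act as a marker of effective intervention. With 42 infants, one nominally significant diffusion result could carry that message.

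**Working it through.** **1. Reproduce the plan's power figures.** Inputs from Power calculations and Analytic strategy: two-sided two-sample t-test, alpha 0.05, equal groups. From the noncentral t distribution:

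| n per group | d | Stated power | Recomputed |
|---|---|---|---|
| 17 | 1.0 | 0.8 | 0.807 |
| 21 | 1.0 | 0.88 | 0.885 |
| 21 | 0.9 | greater than 0.8 | 0.812 |

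The stated figures are right, and they belong to a single unadjusted test.

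**2. Count the comparisons that the text supports.**
- Outcome assessment methods: 1 metric × 2 ages = 2.
- Abstract: 2 metrics × 2 ages = 4.

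Both counts assume one white matter summary per metric and age, that is, no multiplication by tracts.

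**3. Chance of at least one false positive with no treatment effect.** For k independent tests at 0.05 this is 1 − 0.95^k.
- k = 2: 1 − 0.9025 = 9.8%.
- k = 4: 1 − 0.8145 = 18.5%.

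Measurements on the same infants are probably correlated, which lowers these figures. The documents give no correlation, so it is an assumption shown as a range. Simulated two-sided t-tests with 21 per group and a common correlation between all measures gave:

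| Correlation | MD, 2 ages (k = 2) | MD and FA, 2 ages (k = 4) |
|---|---|---|
| 0 (formula) | 9.8% | 18.5% |
| 0.3 | 9.6% | 17.5% |
| 0.5 | 9.1% | 15.7% |
| 0.7 | 8.3% | 13.2% |

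This gives about 8–10% for MD and 13–19% with FA. At a correlation of 0.8 the figures are a little lower, 7.9% and 11.7%.

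**4. Tracts, as illustration only.** If t segments were each tested for MD at both ages, k = 2t. With independent tests the risk first passes 50% at k = 14, that is 7 segments: 1 − 0.95^14 = 51.2%. With MD and FA, k = 4t, and 4 segments give 1 − 0.95^16 = 56.0%. For those 16 tests, a correlation of 0.5 lowers the figure to about 38% and a correlation of 0.8 to about 21%. The article supports none of these segment counts.

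**5. Power under the remedy.** Holm over two ages judges the smaller p-value at 0.05/2 = 0.025 and, if that is significant, the other at 0.05. With 21 per group at the 0.025 step:
- d = 1.0: power 0.81 (0.885 at 0.05).
- d = 0.9: power 0.72 (0.81 at 0.05).

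At alpha 0.025, 80% power at d = 1.0 needs 20.3, so 21 per group. Planned enrolment just meets the 0.8 target at d = 1.0, before any lost scans.

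**The case against.** The case on the other side has several parts.

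- **The metric is named.** The Background hypothesis and Outcome assessment methods both use MD alone, so the conflict comes down to one phrase in the abstract. This is correct, and it is why the remedy is easy. It does not remove the conflict or the two ages.
- **A 0.05 level does not rule out adjusted p-values.** An analysis plan that is not shown may contain a correction. That is possible. But the article states a flat threshold for all analyses without qualification, and a reader following it would test each comparison at 0.05.
- **The hypothesis has a direction.** Counting only results in one direction roughly halves the risk: 1 − 0.975² = 4.9% for MD at two ages if independent, and 1 − 0.975⁴ = 9.6% for four tests. This is fair for a claim of lower MD. The planned tests are two-tailed, however, and FA has no stated direction.
- **The comparison sentence covers short-term white matter outcomes only.** Read literally, it leaves out the 12-month scan. But the aims and the outcome definition include that scan, so this is one more wording to reconcile.
- **These are secondary outcomes.** Whether they need family-wise control is partly convention. That limits the weight of the point.

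A reader might go further and infer that a false-positive white matter claim is likely, with figures such as 64% for 20 tests or 87% for 40. Those need an assumed 10 tracts and independent tests. The tractography section describes processing and does not make each segment a confirmatory test. Nor do the four computed metrics or the two b-values count as endpoints: the first are outputs of the fitted model and the second are acquisition settings.

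**Conclusion.** The point holds in limited form. As written, the article applies an unadjusted 0.05 to a secondary outcome with at least two comparisons, and its sections disagree on whether there are two or four. The resulting risk of at least one false-positive white matter result is about 8–10% for MD, or 13–19% with FA. This assumes two-sided tests, no treatment effect, one white matter summary per metric and age, and correlations from 0 to 0.7. The risk would rise if several segments were tested, by an amount that the article does not allow anyone to compute. The primary language comparison is not affected. The disagreement between the abstract and the outcome definition is an error in the text shown, whatever a separate analysis plan contains.

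**What to change.** 1. Make MD the single secondary metric in every section, and correct the abstract to match the Background and Outcome assessment methods.
2. Apply Holm across the two ages. Alternatively, pre-name one age as the formal test. In either case, align the short-term wording in Analytic strategy with the choice.
3. Label FA, radial and axial diffusivity and single-tract results exploratory, with false-discovery-rate control if several tracts are tested.
4. Replace the blanket statement that 0.05 applies to all analyses with wording that reflects items 1 to 3.
5. Restate power for the diffusion outcome.

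**Cost.** Items 1 to 4 need only changes of wording, but they reduce the number of formal claims. Under Holm, power at the 0.025 step with 21 per group falls to 0.81 at d = 1.0 and 0.72 at d = 0.9, so the claim of power above 0.8 at d = 0.9 would no longer hold for this outcome. Pre-naming one age keeps the stated power but gives up a formal claim at the other. If the sponsor also wants MD averaged over one pre-named tract set, that is a scientific decision, not an edit: it limits multiplicity but could dilute an effect confined to one tract.

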#### Randomization and RCT design elements

Eligible participants will be randomized by the principal investigator ([name]), who will not be blinded, in order to provide close monitoring of the procedures. The principal investigator will allocate participants sequentially as they are enrolled to either the T or the C group using the minimization algorithm by Pocock and Simon [41] implemented in the R statistical software package [42]. Randomization will be stratified for (1) GA (24-0/7 to 27-6/7 weeks or 28-0/7 to 31-6/7 weeks), to control for potential development differences in response to the intervention and as a proxy for neural injury, and (2) socioeconomic status (SES) (above versus below average SES; based on Hollingshead Index (HI) [36, 43]), to control for potential differences in language outcomes affected by socioeconomic factors. Taking into account ethical considerations and parental preferences, twins and multiples will be assigned to the same group [44]. Families and research and clinical staff will be blinded to the group status. In the unlikely event that a family, research staff, or clinical staff suspect that an infant may not tolerate the speech recording, the principal investigator will reveal the group assignment.

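### The stated power (0.88 at d = 1.0, above 0.8 at d = 0.9) is computed on enrolled infants as if all 42 were independent and complete at 18 months, which the protocol itself does not expect

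*Protocol article*

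**What the plan says.** Power calculations gives three statements: 17 infants per group for power 0.8 at d = 1.0; the "planned enrollment of 21 participants per group will yield a power of ß = 0.88 to detect an effect size at that level"; and, at d = 0.9, "a planned enrollment of 21 per group will still yield a power greater than 0.8 to detect a treatment effect". All three are tied to enrolment. The same section fixes the threshold: "The significance level is *p* < 0.05 for all analyses". Analytic strategy names the test for balanced groups: "we will use independent t-tests (two-tailed) to compare T versus C groups on the primary long-term language outcome".

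Other sections describe a trial in which the number analysed may be smaller, or the infants not independent:

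- Outcome assessment methods sets the primary outcome at 18 months adjusted age. Enrolment takes place before hospital discharge.
- Participant retention plan provides a contact at 6 months, and Analytic strategy turns to mixed models partly because of missing data.
- Randomization and RCT design elements states that "twins and multiples will be assigned to the same group".
- Analytic strategy adds that, if multiples are unevenly spread between arms, the group analyses keep the singletons and one randomly chosen infant per set.

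Limitations of the study says: "If we fail to find long-term effects of the intervention, it may be that naturalistic maternal speech overwhelms the effects of the intervention". It adds that such findings would point to further interventions in the first year. It does not mention sample size or precision.

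**The concern.** Power depends on the amount of independent information analysed, not on the number enrolled. Loss over more than a year of follow-up, correlated siblings within an arm, and dropping co-siblings all act in the same direction. If the printed figures assume none of these, readers are told that the trial is better protected against a false negative than it is, most clearly at d = 0.9. The error would carry into interpretation: with power believed to be 0.88, a non-significant result invites a substantive explanation such as later speech exposure, when imprecision may be enough to explain it.

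**Working it through.** **Inputs from the protocol article.** Two-sided alpha 0.05 and an independent-samples t-test; d = 1.0 and d = 0.9; 21 enrolled per arm, 1:1. No loss rate, share of multiples or sibling correlation (ICC) is given, so those below are assumptions.

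**Method.** Exact power from the non-central t distribution with 2n − 2 degrees of freedom and non-centrality d × √(n/2), n being the effective number per arm.

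**Reproducing the plan.** For n = 21 the non-centrality is 1.0 × √10.5 = 3.24 at d = 1.0 and 0.9 × 3.24 = 2.92 at d = 0.9, giving power 0.885 and 0.812. For n = 17 at d = 1.0, power is 0.807. These match the stated 0.88, above 0.8, and 0.8. The smallest n per arm that reaches 0.80 is 17 at d = 1.0 and exactly 21 at d = 0.9.

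**Fewer effective infants (no assumed rate needed).**

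| n per arm | d = 1.0 | d = 0.9 |
|---|---|---|
| 21 | 0.885 | 0.812 |
| 20 | 0.869 | 0.792 |
| 19 | 0.851 | 0.770 |
| 18 | 0.830 | 0.746 |
| 17 | 0.807 | 0.721 |
| 16 | 0.781 | 0.693 |

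The margin for 0.80 at d = 1.0 is (21 − 17)/21 = 19%.

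**Loss alone (assumed 10–20%).** n = 21 × 0.9 = 18.9 gives 0.849 and 0.768. n = 21 × 0.8 = 16.8 gives 0.802 and 0.715. The last case uses a fractional n; whole infants give the rows for 17 or 16 above.

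**Loss plus sibling correlation.** With a share s of infants in twin pairs, the design effect is about 1 + s × ICC, and the effective n is 21 × (1 − loss)/(1 + s × ICC). This applies to an analysis that respects the pairing.

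- Mild case (s = 20%, ICC 0.3, loss 10%): design effect 1.06, n = 18.9/1.06 = 17.83, power 0.826 and 0.742.
- Severe case (s = 30%, ICC 0.7, loss 20%): design effect 1.21, n = 16.8/1.21 = 13.88, power 0.718 and 0.626.

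**One infant per set instead.** n = 21 × (1 − s/2). With no loss, s = 20% gives n = 18.9 (0.849 and 0.768), and s = 30% gives n = 17.85 (0.827 and 0.743). The conditional rule in Analytic strategy therefore also lowers power.

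**Precision.** The effect detectable with 80% power is 0.89 SD at 21 per arm and 0.99 SD at 17. The half-width of the 95% confidence interval is t(0.975; 2n − 2) × √(2/n): 0.62 SD at 21 and 0.70 SD at 17. With all 42 complete and independent, power is 0.72 at d = 0.8 and 0.35 at d = 0.5.

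**The case against.** Several points for the plan are sound.

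- **The arithmetic is right.** A reader might infer a calculation error; there is none. The fault lies in the number to which the formula is applied.
- **There is a margin.** The plan needs 17 per arm for 0.80 at d = 1.0 and enrols 21. A reader might infer that the trial falls below 0.80 at its design effect. Under loss alone that does not follow until about 19% are lost. But the text does not use the extra infants as a reserve: it uses them to claim 0.88 and to cover d = 0.9, and they cannot do that and absorb loss as well.
- **The larger drops rest on assumptions.** The documents establish the direction of the shortfall, not its size. The outcome is a parent questionnaire by web or mail with a retention contact, so 20% loss is not established, and ICC 0.7 is the top of the assumed range.
- **The d = 0.9 case is only an illustration.** It is still a definite statement, and one infant lost per arm makes it untrue.
- **The Limitations text is hedged.** A reader might infer that the plan would treat a null result as proof of no lasting benefit. It does not say so: it opens by allowing that the intervention may not change outcomes and offers later speech as a possibility. What stands is that imprecision is missing from the explanations offered.

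Two further inferences should be resisted. The trial is not limited to detecting effects of 0.9–1.0 SD: that is roughly the effect found with 80% power, and an observed difference of about 0.62 SD would already be significant at 21 per arm. The two scores in the primary outcome raise a separate multiplicity question, on which this point does not rely.

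**Conclusion.** The point holds in limited form. The stated powers are correct for 42 independent infants with complete outcomes, but are presented as properties of the enrolled sample, in a protocol that foresees missing data, co-assigned siblings and possible exclusion of siblings. Without any assumed rate, one infant lost per arm takes the d = 0.9 figure to 0.792, below the claimed level, and the d = 1.0 figure from 0.885 to 0.869. Power of 0.80 at d = 1.0 holds down to 17 effective infants per arm and not below.

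The wider ranges are conditional. Loss of 10–20% alone gives about 0.85–0.80 at d = 1.0 and 0.77–0.72 at d = 0.9. Adding 20–30% of infants in twin pairs with ICC 0.3–0.7 gives about 0.83–0.72 and 0.74–0.63. With an interval half-width of 0.62–0.70 SD, a non-significant result would often be compatible with a moderate benefit and could not by itself be attributed to later speech exposure.

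**What to change.** In Power calculations:

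- Restate power for the expected number analysed, adjusted for siblings, showing the assumed loss, share of multiples and ICC as ranges.
- Say that the step from 17 to 21 per arm covers loss for 0.80 at d = 1.0 only.
- Replace the d = 0.9 sentence with the power at the expected number, or with the effect detectable with 80% power (0.89 SD at 21 per arm, 0.99 SD at 17).

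In Limitations of the study, add limited precision as an alternative explanation of a non-significant result, and commit to reporting that result with its confidence interval.

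This is rewording only, with no change to enrolment or conduct. The cost is a less favourable stated power.
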